### Study design

The Platelet-Rich plasma Injection Management for Ankle OA (PRIMA) study is a multicentre, stratified, block‐randomised, double‐blind, placebo‐controlled trial design will be conducted in order to compare two treatment groups: PRP versus placebo (saline). After the 26 weeks follow-up of the last patient in the study, the principal investigator and coordinating researcher will be unblinded only after the analysis of the primary outcome. A flow chart of the design and follow-up is shown in figure 1. The study included its first patient in August 2018 and aims to include the last patient by January 2021, consequently allowing analysis and then deblinding to commence after the last follow-up (26 weeks) of the last patient by July 2021.

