### Randomisation, blinding and treatment allocation

We will include patients at the centre of their first outpatient clinic appointment. For each patient the coordinating researcher will prepare a syringe with PRP and a syringe with placebo (isotonic saline: 0.9% sodium chloride). A Good Clinical Practice (GCP) approved data management system (Castor EDC, based in Amsterdam, the Netherlands) will be used to perform a computer-generated block randomisation scheme with patients stratified to centre with a variable block size of 2, 4 or 6. This procedure will ensure treatment allocation concealment. The coordinating researcher, treating physician and patient all remain blinded to the allocated intervention. An independent researcher from the coordinating location will have access to the randomisation result and the allocated intervention. This will be relayed to a GCP-certified research assistant at the centre. The research assistant then selects one of the two syringes based on the allocated intervention and blinds the syringe with a covering sheath, ensuring concealment of the content of the syringe. The patients, treating physicians and coordinating researcher will all be blinded to the allocation of the intervention and to the contents of the syringe. The success of blinding will be assessed by asking patients which injection they think they have received just after the injection procedure, this will then be registered accordingly.

After the 26 weeks follow-up of the last patient in the study, the principal investigator and coordinating researcher will be unblinded only after the analysis of the primary outcome. The patients will remain blinded to the therapy until the 52 weeks follow-up (online supplementary appendix 1) of the last patient in the study.

10.1136/bmjopen-2019-030961.supp1Supplementary data

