### Use of co-intervention

Patients are instructed to avoid the use of co-interventions and non-steroidal anti-inflammatory drugs if possible, 24 hours prior to the intervention and if possible up to a year after the first injection. Throughout the study, key treatment (including usual care: exercise therapy and healthy lifestyle advice) and co-interventions used by patients will be registered, such as non-steroidal anti-inflammatory drugs, other analgesic drugs, intra-articular injections or inlays.

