### Inclusion

Patients are recruited for inclusion by their treating physicians at location. Following inclusion PRP will be prepared according to the PRP system instructions of the manufacturer. During the first two consultations, a total of two intra-articular injections will be documented with a time interval of 6 weeks. The patient will have no additional costs to usual care as a result of taking part in this study.

Physical examination will be performed on three occasions up to 26 weeks from baseline. Patient-reported outcome measures (PROMs) will be used to evaluate the treatment effect up to 5 years. A cost-effectivity analysis will be performed at 1 year using the PROductivity and DISease Questionnaire (PRODISQ). The time-frame of the follow-up questionnaires is further illustrated in table 1. Questionnaires will be managed and distributed digitally using a GCP-approved data management system (Castor EDC).

**Table 1 T1:** Time-frame of the follow-up questionnaires

Follow-up	
Baseline	First intervention injections Physical examination AOFAS PROMs PRODISQ cost-effectivity
6 weeks	Second intervention injection Physical examination AOFAS PROMs
12 weeks	AOFAS PROMs PRODISQ cost-effectivity
26 weeks	AOFAS PROMs PRODISQ cost-effectivity
39 weeks	PRODISQ cost-effectivity
52 weeks	AOFAS PROMs PRODISQ cost-effectivity
5 years	AOFAS PROMs

In addition to the AOFAS score, the following PROMs will be taken: FAOS, AOS, VAS, AAS, SF-36, GAS, EQ-5D-3L. These PROMs will be elaborated on further on. Furthermore, PRODISQ will be used to perform a cost-effectivity analysis. These questionnaires can be found in online supplementary appendix 1.

AAS, Ankle Activity Score; AOFAS, American Orthopaedic Foot and Ankle Society; AOS, Ankle Osteoarthritis Score; EQ-5D-3L, EuroQol-5 dimensions-3 levels; FAOS, Foot and Ankle Outcome Score; GAS, Global Attainment Scaling; PRODISQ, PROductivity and DISease Questionnaire; PROM, patient-reported outcome measures; SF-36, subjective patient satisfaction Short Form Health Survey-36; VAS, Visual Analogue Scale.

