### Secondary outcome measures

To test for the effect of treatment on between-group differences in secondary outcomes, we will use the repeated measurement general linear model. Changes from baseline to all follow-up time points will be included in the model.

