## Discussion

This is the first study evaluating the efficacy and cost-effectiveness of PRP injections in the treatment of ankle OA with a multicentre, stratified, block-randomised, double-blind, placebo-controlled design. The primary outcome is the AOFAS score at 26 weeks. Our study will also evaluate the long-term efficacy of PRP for up to 5 years.

PRP has been shown to alleviate symptoms of patients suffering from knee OA.^11^ In the absence of effective evidence-based non-surgical interventions for ankle OA, PRP would fulfil a clear clinical need. Previous trials concerned with the efficacy of PRP for multiple indications are usually of low quality and adhere to a follow-up of 26 weeks or shorter. Furthermore, a cost-effectiveness analysis has never been performed in previous trials on PRP in the treatment of OA.

A positive study outcome would have a significant impact leading to change in clinical practice, where PRP could be offered as a non-surgical intervention. A negative outcome will prevent the widespread use of a non-efficacious treatment.

This study has potential limitations. First of all, due to financial constraints (semi-quantitative), MRI-defined cartilage degenerative changes will not be used as a secondary outcome score. Furthermore, the composition of PRP is not analysed. This decision is based on the fact that PRP preparation and composition has frequently been analysed and is typically not performed in clinical practice prior to injection.^27^ The PRP we use (Hettich Rotofix32 A centrifuge and Arthrex syringes) is one out of a multitude of commercially available PRP products. All these products differ in their production method and content, and different treatment regimens regarding dose, timing and number of injections are used in clinical practice. The generalisability to other PRP products and treatment regimens remains unknown.

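### No 5-year outcome is covered by the guarantee of patient blinding, yet the 5-year data are presented as long-term efficacy in a double-blind trial and enter the same secondary-outcome model as the blinded visits

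*Protocol article*

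**What the plan says.** The section *Randomisation, blinding and treatment allocation* sets two unblinding times. For study staff, "the principal investigator and coordinating researcher will be unblinded only after the analysis of the primary outcome"; that analysis follows the last patient's 26-week visit. For patients: "The patients will remain blinded to the therapy until the 52 weeks follow-up (online supplementary appendix 1) of the last patient in the study".

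The calendar is in *Study design*: "The study included its first patient in August 2018 and aims to include the last patient by January 2021".

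The 5-year data are described as follows.
- *Inclusion*: "Patient-reported outcome measures (PROMs) will be used to evaluate the treatment effect up to 5 years". Table 1 lists AOFAS and the other PROMs at 5 years.
- *Secondary study parameters/end points*: total AOFAS at 5 years is a named secondary outcome.
- *Discussion*: "Our study will also evaluate the long-term efficacy of PRP for up to 5 years". This stands in the same paragraph that calls the design double-blind and placebo-controlled.
- *Secondary outcome measures* (analysis): "Changes from baseline to all follow-up time points will be included in the model".

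The trial is called double-blind in the strengths and limitations box, in *Study design* and in the *Discussion*, each time without a time limit. The limitations paragraph of the *Discussion* does not mention that blinding has ended by the 5-year visit.

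**The concern.** The 5-year outcomes are mainly patients' own reports of pain, function and quality of life, which are sensitive to knowing whether one received PRP or saline. If that knowledge is open to patients before every 5-year assessment, a difference between arms at 5 years mixes any effect of treatment with the effect of knowing the allocation.

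Little in the design offsets this. *Inclusion* schedules physical examination only up to 26 weeks. The only stated check of blinding is the patient's guess just after the injection procedure, which is uninformative about year 5. *Ethics and dissemination* says patients will be told the trial results, although it gives no date. The request to avoid co-interventions runs only "if possible up to a year after the first injection", and the product is one already used in practice, so later treatment could also differ between arms.

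At stake is what the trial may claim at 5 years. As written, an unblinded comparison would be reported under a double-blind label and modelled together with visits at which patients were blinded.

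**Working it through.** **Inputs** (*Study design*; *Randomisation, blinding and treatment allocation*; Table 1): first inclusion August 2018; last inclusion by January 2021; patient blinding guaranteed to the last patient's 52-week visit; final assessment 5 years after inclusion. Only months are given, so each date is carried as a range from the first to the last day of the month.

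**Step 1. Reproduce the stated date.** Last inclusion + 26 weeks (182 days): 1 January 2021 gives 2 July 2021, and 31 January 2021 gives 1 August 2021. The article says "last follow-up (26 weeks) of the last patient by July 2021". The method reproduces its figure.

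**Step 2. End of guaranteed patient blinding.** Last inclusion + 52 weeks (364 days): 31 December 2021 to 30 January 2022, so about January 2022.

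**Step 3. Window of 5-year assessments.**
- First patient: August 2018 + 5 years = August 2023.
- Last patient: January 2021 + 5 years = January 2026.

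**Step 4. Gap between the two.**
- First patient: January 2022 to August 2023 = 19 months. The extremes are 30 January 2022 to 1 August 2023 (18 months) and 31 December 2021 to 31 August 2023 (20 months).
- Last patient: January 2022 to January 2026 = 48 months.
- Cross-check by patient: the first is covered for about 41 months (August 2018 to January 2022), and 60 − 41 = 19; the last is covered for about 12 months, and 60 − 12 = 48.

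The number of 5-year assessments inside the guaranteed blinded period is therefore zero.

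**Step 5. How far recruitment would have to slip.** A 5-year visit falls before the end of patient blinding only if last inclusion + 52 weeks is later than the first 5-year visit. August 2023 − 52 weeks gives 2 August to 1 September 2022. That is 18 to 20 months after the planned last inclusion, and it would rescue only the earliest patients.

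**Step 6. Place in the secondary model.** Table 1 gives five follow-up time points with AOFAS and PROMs: 6, 12, 26 and 52 weeks, and 5 years. The first four lie within guaranteed patient blinding and the fifth does not. If the model were used for an equally weighted average over time (an assumption; the article does not say), the 5-year visit would carry 1/5 = 20% of it. If it gives visit-specific contrasts, the 5-year data would bear largely on the 5-year estimate alone.

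**The case against.** The strongest reply is that nothing is hidden. The article states when patient blinding ends, that period covers the 26-week primary outcome, the patient-reported 52-week outcomes and the 1-year economic analysis, and no sentence says in terms that the 5-year data are double-blind. On this view only a clarification of wording is due. The disclosure does stand, and unblinding patients after 52 weeks may be a reasonable choice. But the reader is told of a double-blind design and of 5-year efficacy in one paragraph with no qualification, and the analysis text does not separate the 5-year visit from the others. That affects the conclusion as well as the wording.

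Four stronger readings are tempting, and the article does not support them.
- *The primary test is contaminated.* The primary-outcome section also refers to all follow-up time points, so a reader might infer this. But the primary analysis follows the last 26-week visit (about July 2021) and the first 5-year visit is in August 2023. *Statistical analysis* also bars changes to the interpretation once groups are unblinded.
- *The 5-year comparison is fully open-label.* The word *until* ends a guarantee; it does not say that every patient will be told. The supplementary appendix cited there is not shown, and no unblinding date is given for treating physicians.
- *Later injections go unrecorded.* *Use of co-intervention* registers co-interventions throughout the study and names intra-articular injections. Surgery is not among its examples. Actual crossover to PRP is a possibility, not something the article establishes.
- *A 5-year safety claim is compromised.* No section presents 5-year adverse events as a placebo-controlled comparison.

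**Conclusion.** The point holds for the 5-year secondary comparison and only there. On the planned dates every 5-year AOFAS and PROM assessment falls 19 to 48 months after guaranteed patient blinding ends, and a recruitment delay of less than about 18 months would not change that. A 5-year difference therefore cannot be read as efficacy under patient blinding.

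The size and direction of any bias cannot be derived from the article. Knowledge of allocation could favour PRP, while later PRP use in the saline arm would act the other way. How far the 5-year data would influence other secondary results depends on the contrast taken from the model, which may be left to an analysis plan not shown.

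The conclusion assumes that recruitment broadly followed the stated calendar and that the unseen appendix does not extend patient blinding. Unblinding of the principal investigator and coordinating researcher before some 52-week visits is a separate matter and is not judged here.

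**What to change.** 1. In the strengths and limitations box, *Inclusion* and the *Discussion*, state that the patient-blinded comparison ends at 52 weeks.
2. In *Secondary outcome measures*, limit the treatment model to visits up to 52 weeks. Analyse the 5-year AOFAS and PROMs separately and label them an unblinded, exploratory follow-up.
3. Add one item to the existing 5-year digital questionnaire: does the patient know which injection was given? Report the answers by arm, next to the later injections already registered under *Use of co-intervention* and any later ankle surgery.

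This needs no extra patients or visits and leaves the primary analysis unchanged. The cost is some redrafting, one questionnaire item, one separate analysis and a weaker label on the 5-year result.

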### Intervention

In this study, patients will be randomised into two treatment groups: PRP injection or placebo saline injection. For each patient, the coordinating researcher will prepare a PRP and a placebo injection (isotonic saline: 0.9% sodium chloride). The PRP syringe will be prepared according to the instructions of the manufacturer.^12^ Prior to commencement of the study, the coordinating researcher was trained by a representative of Arthrex, as well as two experienced members of the PRIMA trial research group (GR and [name]) with a vast scientific experience regarding PRP preparation and injection.^12 13^ The PRP will be prepared using a widely used and commercially available system (Arthrex double syringe PRP system, Arthrex Medizinische Instrumente GmbH, Garching, Germany).

One syringe of 15 mL autologous blood will be collected twice from the cubital vein: at inclusion and at a time interval of 6 weeks. After blood collection the syringe will undergo 5 min of centrifugation and the injection will be given within 30 min following venepuncture to prevent formation of blood clots. No additional substances (calcium, thrombin or citrate) will be added to the PRP solution. For each procedure, 2 mL of PRP or placebo will be prepared and injected into the affected ankle joint under ultrasonographic guidance using a sterile technique. All patients will receive a second injection at 6 weeks, regardless of the effect of the first injection. To guarantee blinding for the allocated treatment of the patient, treatment assessor and treating physician, blood will be drawn and both PRP and placebo will be prepared according to exactly the same procedure for each patient (both at inclusion and at a time interval of 6 weeks after the first injection). However, in the control group, patients will be injected with 2 mL of physiological saline instead of PRP. An unblinded research assistant will blind one of the two identical syringes based on the allocated intervention using a specially manufactured covering sheath in order to conceal randomisation. Following the intra-articular injection, the syringe covered by the sheath (containing either the remnants of the PRP or saline) is handed to the unblinded research assistant, who will dispose of the syringe, therefore keeping the treating physician and coordinating researcher blinded. After the intervention, patients are advised to avoid heavy or repetitive stress to the ankle joint for a period of 48 hours. Furthermore, patients receive a leaflet containing usual-care healthy lifestyle advice beneficial for ankle OA. This includes losing weight and exercise (avoiding heavy or repetitive ankle loading exercises) such as walking, cycling or swimming.

### Use of co-intervention

Patients are instructed to avoid the use of co-interventions and non-steroidal anti-inflammatory drugs if possible, 24 hours prior to the intervention and if possible up to a year after the first injection. Throughout the study, key treatment (including usual care: exercise therapy and healthy lifestyle advice) and co-interventions used by patients will be registered, such as non-steroidal anti-inflammatory drugs, other analgesic drugs, intra-articular injections or inlays.

### Study procedures

In the event the patient meets the criteria for inclusion and exclusion, the patient will be informed in more detail about the study procedure. At that time, the patient can ask questions about the study and decide whether they will participate and sign the informed consent form. Subsequently, the patient will proceed to inclusion and the randomisation procedure.

### Inclusion

Patients are recruited for inclusion by their treating physicians at location. Following inclusion PRP will be prepared according to the PRP system instructions of the manufacturer. During the first two consultations, a total of two intra-articular injections will be documented with a time interval of 6 weeks. The patient will have no additional costs to usual care as a result of taking part in this study.

Physical examination will be performed on three occasions up to 26 weeks from baseline. Patient-reported outcome measures (PROMs) will be used to evaluate the treatment effect up to 5 years. A cost-effectivity analysis will be performed at 1 year using the PROductivity and DISease Questionnaire (PRODISQ). The time-frame of the follow-up questionnaires is further illustrated in table 1. Questionnaires will be managed and distributed digitally using a GCP-approved data management system (Castor EDC).

**Table 1 T1:** Time-frame of the follow-up questionnaires

Follow-up	
Baseline	First intervention injections Physical examination AOFAS PROMs PRODISQ cost-effectivity
6 weeks	Second intervention injection Physical examination AOFAS PROMs
12 weeks	AOFAS PROMs PRODISQ cost-effectivity
26 weeks	AOFAS PROMs PRODISQ cost-effectivity
39 weeks	PRODISQ cost-effectivity
52 weeks	AOFAS PROMs PRODISQ cost-effectivity
5 years	AOFAS PROMs

In addition to the AOFAS score, the following PROMs will be taken: FAOS, AOS, VAS, AAS, SF-36, GAS, EQ-5D-3L. These PROMs will be elaborated on further on. Furthermore, PRODISQ will be used to perform a cost-effectivity analysis. These questionnaires can be found in online supplementary appendix 1.

AAS, Ankle Activity Score; AOFAS, American Orthopaedic Foot and Ankle Society; AOS, Ankle Osteoarthritis Score; EQ-5D-3L, EuroQol-5 dimensions-3 levels; FAOS, Foot and Ankle Outcome Score; GAS, Global Attainment Scaling; PRODISQ, PROductivity and DISease Questionnaire; PROM, patient-reported outcome measures; SF-36, subjective patient satisfaction Short Form Health Survey-36; VAS, Visual Analogue Scale.

### Replacement of individual patients after withdrawal

In the sample size calculation, we compensated for an expected loss of 10% of patients to follow-up. No patients will be replaced after withdrawal.

### Safety

All adverse events reported spontaneously by the patient or observed by the investigator or his staff will be recorded. A variety of conditions have been treated with PRP ranging from muscle and tendon injuries to intra-articular injections of the knee and ankle. To date, no serious adverse events have been documented in the literature, concerning PRP intra-articular injections of the ankle. In accordance with the Central Committee on Research Involving Human Subjects guidelines, this study was classified as low risk for adverse events. Therefore, the local Medical Ethical Commission will be notified of any serious adverse events. In the event this happens, the advice of the Medical Ethical Commission will be followed accordingly.

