## Abstract

**Introduction:**

Platelet-rich plasma (PRP) is a potentially efficacious treatment for ankle osteoarthritis (OA), but its use has not been examined in high-quality studies. Systematic reviews show that PRP injections significantly decrease pain and improve function in patients with knee OA. Ankle OA is more common than hip or knee OA in the young active population; with a prevalence of 3.4%.

PRP injections in ankle OA are shown to be safe and improve quality of life over time, but no randomised controlled trial has been conducted. Our randomised controlled trial will evaluate the efficacy of PRP injections for symptom reduction and functional improvement, compared with placebo, in the treatment of ankle (talocrural) OA.

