**Trial registration number:**

NTR7261.

Strengths and limitations of this studyThis is the first study to evaluate the efficacy and cost-effectiveness of ankle (talocrural) osteoarthritis (OA) in a multicentre, stratified, block-randomised, double-blind, placebo-controlled trial design. A positive study outcome will have a significant effect on widespread availability and nationwide implementation of an intra-articular injection treatment for ankle OA with platelet-rich plasma (PRP). A negative outcome (no effect of PRP), will prevent the widespread use of a non-efficacious treatment on patients.The study population consists only of patients with isolated ankle OA and no concomitant OA in other major joints of the lower extremities that negatively affects their daily activity level.The PRP used in this randomised controlled trial is an available PRP product that is used in clinical practice.There is a multitude of commercial PRP products available that differ in their production method and content, and different treatment regimens regarding dose, timing and number of injections are used in clinical practice. The generalisability to other PRP products and treatment regimens remains unknown.The composition of PRP will not be analysed; this decision was based on the fact that PRP preparation and composition has frequently been analysed and is typically not performed in clinical practice prior to injection.

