Recent systematic reviews on the intra-articular injection therapy in ankle OA found a lack of evidence from high-quality studies to assist in clinical decision-making.^5 6^ When compared with placebo injections, hyaluronic acid or corticosteroid injections, PRP injections might significantly decrease pain and improve function in patients with knee OA.^7–9^ Given the clinical effect on pain reduction in knee OA and a good safety profile, PRP is a promising non-surgical therapy for ankle OA.^10 11^ PRP might delay the irreversible surgical options like arthrodesis. No significant adverse events have been reported in any PRP trials regarding ankle OA, knee OA, acute hamstring injuries or Achilles tendinopathy.^8 12–17^ Clinical studies on PRP in ankle OA are limited to a single report of 5 cases and a prospective case series of 20 subjects, which both showed safety and significant reduction of pain at a mean of 16 months and 12 weeks follow-up.^14 18^ Well-designed prospective randomised controlled trials (RCT) have not yet been performed.

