### Secondary study parameters/end points

Secondary outcome measures are a number of other PROMs. Specific time points of the secondary outcome measures can be found in table 1.

Ankle Osteoarthritis Score (AOS) is a Visual Analogue Scale (VAS) from 0 to 100 mm with 18 questions; 9 relating to pain and 9 relating to disability.Foot and Ankle Outcome Score (FAOS): each question is assigned 0–4 points based on the answer given. The scale runs from 0 (extreme symptoms) to 100 points (no symptoms).In order to evaluate pain, the pain subscale of AOFAS (0–40 points) will be analysed. On this scale, the lower the score the more pain the patient has. Additionally, a VAS score (VAS 0–100 mm) is measured during activities of daily living, with 0 mm being no pain and 100 mm the worst pain imaginable.Total AOFAS score at the other time points than the primary one (at 6, 12 and 52 weeks as well as 5 years).Ankle Activity Score (0–10 points) is scored according to chart based on the performable activity levelSubjective patient satisfaction (four categories): poor, fair, good, excellent.Short Form Health Survey-36 is a health-related quality of life score (0–100 points). The higher the patient scores, the higher the disability.The Global Attainment Scaling is a method of scoring based on achievement related to predetermined goals in agreement with the patient. Points are subtracted for not achieving the predefined goals or vice versa. Scores range from 100 (high functioning) to 0 (severely impaired)EuroQol-5 dimensions-3 levels (EQ-5D-3L) utility score allows a patient’s health to be defined by a 5-digit number.PRODISQ will be used to determine indirect costs and direct costs cost-effectivity. PRODISQ is taken at baseline and every 3 months thereafter up until 1 year. This will be done in conjunction with the EQ-5D-3L.

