### Ethics and dissemination

In the events of amendments or other changes, co-researchers will be notified. If relevant, patients participating will also be notified. Intellectual data will be the property of the PRIMA study group. Participant data that underline the results reported in this article following de-identification will be shared anonymously on request following publication. Data will be shared, wherever legally and ethically possible and in line with ICMJE guidelines, with researchers who provide a methodologically sound proposal. Data will be stored in a repository (Figshare) under management of the medical library of the AMC. Any proposal should contain: title, background, rationale, objective, methods (eligibility criteria, variables and timeframe of interest, statistical plan), information regarding publication including authorship.

The results of this project study and new knowledge will be disseminated through the Dutch Arthritis Association (ReumaNederland), presentations, news publications, blogs, websites, social media and professional organisations (rheumatology, orthopaedics, primary care medicine, sports medicine, public health) and the Dutch patient federation (Patiëntenfederatie Nederland). The patients will also be informed about the results of the study. The study will be conducted according to the principles of the Declaration of Helsinki, GCP and the Medical Research Involving Human Subjects Act (WMO). The board of each participating hospital reviewed and approved the local feasibility. Monitoring and auditing will be carried out throughout the study. In the event of serious adverse events, these will be documented and reported to the monitor and the Medical Ethics board. Eligible patients will be informed of the study and will sign an informed consent form before participating (acquired by researchers associated with the study). Provisions for post-trial care as compensation for those who suffer harm from trial participation is documented in the patient information.

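### Adverse events are captured only by spontaneous report or staff observation and no adverse-event outcome is listed, so mild injection reactions are likely to be under-recorded in both arms

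*Protocol article*

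**What the plan says.** The Safety section of the protocol article sets the method of capture: "All adverse events reported spontaneously by the patient or observed by the investigator or his staff will be recorded". It adds that "this study was classified as low risk for adverse events". For serious events, Safety provides for notifying the medical ethics committee, and Ethics and dissemination says that "these will be documented and reported to the monitor and the Medical Ethics board".

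The primary outcome is the AOFAS score at 26 weeks. The secondary section opens with "Secondary outcome measures are a number of other PROMs" and then itemises scales, patient satisfaction, quality of life and a cost questionnaire. Neither section names an adverse-event outcome.

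On earlier evidence, the abstract states that "PRP injections in ankle OA are shown to be safe and improve quality of life over time". Background and rationale says that "Clinical studies on PRP in ankle OA are limited to a single report of 5 cases and a prospective case series of 20 subjects".

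**The concern.** The treatment is an intra-articular injection given twice, six weeks apart. The reactions to expect most often are local and short-lived. A method that waits for the patient to volunteer an event, or for staff to notice one, suits serious events better than a sore or swollen joint that has settled before the next visit.

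The Safety section states this method outright, so it can be judged as written. A detailed analysis plan elsewhere could not recover events that nobody asked about. What is at stake is the tolerability record of a trial that describes itself as the first randomised evaluation of PRP in ankle osteoarthritis. A short list of reported events could be taken to show good tolerability when it partly reflects how events were collected.

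**Working it through.** **Setting the sections side by side**

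1. *Method.* Safety names two routes, spontaneous report and observation. It names no checklist, diary or standard question.
2. *Timing.* Under Intervention, the second injection follows at 6 weeks. In Table 1 (under Inclusion), the next entry after the first injection is week 6, and the next after the second is week 12. The table is titled as a schedule of questionnaires, so it does not rule out other contacts, but the article describes no adverse-event enquiry at any contact.
3. *Opportunities to observe.* Under Loss to follow-up, the coordinating researcher contacts every patient and attends every visit, with the stated purpose of limiting dropout. Use of co-intervention registers analgesics and other treatments, not reactions. The Inclusion text gives three physical examinations up to 26 weeks, while Table 1 shows them only at baseline and 6 weeks. Those two statements need reconciling. On either count, the examinations are not described as adverse-event questioning.
4. *Outcome list.* It is itemised down to satisfaction categories and costs, and adverse events are absent from it.

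**What under-recording does to a comparison**

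The article gives no adverse-event figure to reproduce. The only input taken from it is 50 patients per arm (Sample size). All rates and capture fractions below are assumptions.

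Let p1 and p0 be the true proportions with a reaction, and c the fraction captured, equal in both arms because of blinding. The recorded proportions are c·p1 and c·p0, so the recorded difference is c·(p1 − p0). The ratio is unchanged. Take p1 = 0.30 and p0 = 0.10. Power is the sum, over all tables with 50 per arm that give two-sided Fisher p ≤ 0.05, of their binomial probabilities:

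| Capture c | Recorded rates | Recorded difference | Power |
|---|---|---|---|
| 100% | 30% vs 10% | 20 points | 0.64 |
| 75% | 22.5% vs 7.5% | 15 points | 0.45 |
| 50% | 15% vs 5% | 10 points | 0.24 |

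A normal-approximation formula gives 0.71, 0.56 and 0.38. The levels differ, but the decline has the same direction.

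The chance of recording at least one event among 50 PRP patients is 1 − (1 − c·p)^50:

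| True rate p | c = 100% | c = 50% | c = 25% |
|---|---|---|---|
| 5% | 92% | 72% | 47% |
| 2% | 64% | 40% | 22% |

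With no events in 50 patients, the exact two-sided 95% upper limit is 1 − 0.025^(1/50) = 7.1%. That limit applies to the true rate only if capture is complete.

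**The case against.** The strongest reply is that spontaneous-or-observed recording is a deliberate choice in a study classified as low risk. Staff see every patient, analgesic use is registered, and events are recorded in two randomised, blinded arms. The sample size was set for the AOFAS score, and even with full capture the illustrative power is only 0.64, so the collection method is not the only limit. Much of this stands. It means that observation is planned rather than accidental, that bias in direction is not the main worry, and that the point is moderate in weight. It does not supply a question that elicits a reaction already resolved.

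Four stronger readings are tempting, and the article does not support them.

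- *That no between-arm safety analysis is planned.* The analysis section says only "To test for the effect of treatment on between-group differences in secondary outcomes, we will use the repeated measurement general linear model", but a condensed article commonly leaves adverse-event tables to the full protocol or SAP, which are not shown.
- *That the trial claims safety grounds for adoption and cannot back them.* The sentence "A positive study outcome will have a significant effect on widespread availability and nationwide implementation" depends on a positive outcome, and the hypothesis concerns efficacy only.
- *That there will be no controlled estimate of harm, or that reactions to the two injections cannot be told apart.* Events are recorded in both arms, and nothing says that they are undated.
- *That the earlier ankle data amount to no events in 25 patients, with an upper limit of 1 − 0.025^(1/25) = 13.7%.* The article speaks of no significant adverse events and no serious ones. It gives no count of mild reactions, so that limit does not apply to them.

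**Conclusion.** The concern holds in a limited form. Capture as stated is passive, no solicited question is described, and no adverse-event outcome is listed. Mild, short-lived reactions to either injection are therefore likely to be under-recorded in both arms. This reduces any absolute difference and limits what can be concluded about tolerability. Serious events have their own reporting route and are less affected.

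The size cannot be derived from the article. The power figures illustrate the mechanism under assumed rates and equal capture in the two arms, and should not be quoted as estimates for this trial. The efficacy conclusions are untouched.

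Separately, the abstract's statement that safety has been shown is strong for ankle evidence of 5 + 20 = 25 uncontrolled patients. The article also cites PRP trials in knee osteoarthritis, hamstring injury and Achilles tendinopathy, but these are not evidence from the ankle.

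**What to change.** 1. **Safety:** keep spontaneous and observed reports, and add one short standard adverse-event question with start and stop dates, worded identically in both arms. The blinded researcher asks it at the 6-week visit before the second injection. It is repeated in the existing digital questionnaires at 12, 26, 39 and 52 weeks.
2. **Secondary study parameters/end points:** list, as a descriptive outcome, the number and proportion of patients per arm with any adverse event, any injection-related event and any serious event. State that these are tabulated and not entered in the repeated-measures model used for the scales.
3. **Abstract:** qualify the safety statement by the 25 uncontrolled ankle patients.

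The cost is one short form in the existing data system, one table, a minute or two of patient time per contact and more minor events to process. The change does not remove reliance on memory: a reaction in the first days after an injection would still be recalled up to six weeks later.
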